**Fig. 2 Fig2:**
[figure not shown]
Timeline of Ambulatory Assessment

The second test appointment (T2) will again take place in our facilities and the TSST will be carried out with the participants. Due to the hormonal circadian rhythm and to record greater cortisol responses, all participants will be tested in the afternoon [21]. Furthermore, 8 saliva samples and 9 mood assessments will be taken to capture the psychological and endocrinological stress reactions. Directly after arrival of the participants, the first saliva sample will be taken and the sensor for measuring the heart rate will be attached (about 20 min after arrival). The participants can come to rest by filling out questionnaires and using relaxation material. This will be followed by the TSST, whereby VR glasses or eye-tracking glasses will be first put on, calibrated, and tested before the preparation period of the TSST (5 min) starts. Then, the participants will be confronted with a speech (“Why are you suited for the position of student representative?”) and an arithmetic task (e.g., for 11-year-old participants: “Please count backwards from the number 785 in steps of 7.”) in front of a panel and a camera. Both tasks will be adapted to the age of the participants and last 5 min each. In the TSST-IV, the panel will consist of one female and one male staff member of the department, who have been specially trained to keep gestures, facial expressions, and feedback neutral. Based on the real version, we will use one male and one female virtual human in the TSST-VR. We designed the virtual humans using the computer graphics software Daz3D [22]. We used the characters Genesis 8 Male and Genesis 8 Female [23] and adapted their appearance (body shape, facial expressions, skin, lip synchronization) by morph targets and textures to match the skin type and basic appearance to the real panel members in the TSST-IV. The virtual humans can give visual (taking notes) and auditory (e.g., “Error, please start again.”) feedback that can be triggered by the experimenter via keyboard. These feedback options are similar to the reactions of the panel in the real version. We implemented the VR application using the Unity3D game engine (v. 2019.3.11f1) and modelled a virtual replica of the real environment with identical room dimensions (width: 5.82 m, length: 5.85 m) using the computer graphics software Blender [24] (Fig. 3). We included 3D models of all objects placed in the real environment to ensure the virtual space consists of the same accessory with the same number of potential distractors. To register fixations of the gaze behavior, we defined five 3D Areas of Interest (AOI) using invisible bounding boxes around the male and female virtual human’s face and body, and the camera. We used the maximum bounding box of each AOI to define the *x*, *y*, and *z* dimensions [25]. To immerse the participants in the virtual environment, they will be fitted with an HTC Vive Pro Eye Head Mounted Display (HMD). The HMD has a wide horizontal field of view of 110° and a spatial resolution of 1440 × 1600 pixels per eye. All audio files will be presented via the HMD’s headphones. Participants in VR will perceive the surrounding environment from first-person perspective. The VR application will run on a Dell G5 15 notebook PC (Windows 10, Intel i7-8750H, 8GB RAM, NVIDIA GeForce RTX 2060 Mobile graphics card).

**Fig. 3 Fig3:**
[figure not shown]
Comparative presentation of the Trier Social Stress Test in vivo (**A**) and in virtual reality (**B**)

The real or virtual TSST will immediately be followed by the 5-min relaxation phase via the smartphone app. The participants shall relax as practiced in the AA. Therefore, in the control group they should sit calmly and relaxed and in the intervention group they should relax by breathing with the help of the smartphone app. Afterwards, they shall use the remaining time to answer further questionnaires at rest. During the debriefing, particular attention will be paid to conveying to the participants that the committee of the TSST was only trained personnel of the research team or programmed avatars. They were supposed to behave in this way regardless of the performance of the participant. It will be made clear that it was not a measurement of individual performance but of psychosocial stress. In total, this appointment will take approximately 2 h. An overview of the procedure for the second test date is shown in Fig. 4.

**Fig. 4 Fig4:**
[figure not shown]
Timeline of the second test date. S, Salivary Sample; TSST, Trier Social Stress Test

### Criteria for discontinuing or modifying allocated interventions {11b}

If the diagnostic instruments used to check the inclusion criteria show abnormalities during the telephone screening (T0) or at the first appointment (T1) and exclusion criteria are thus met, study participation will be discontinued at this point and the person will be excluded from further study participation.

During the telephone screening (T0), participants will be asked in advance if they have ever suffered from severe motion sickness (e.g., “Have you ever been sick on a ship or while reading a book in a car?”) as an indicator for VR sickness. If so, the participants will be excluded from the TSST-VR condition and assigned to the TSST-IV group. Regarding the change between TSST conditions, there are no other reasons besides severe motion sickness that will lead to a change between groups.

### Strategies to improve adherence to interventions {11c}

For each survey in the AA, there will be a narrowly defined time period during which participants can answer questions. The participants will receive a notification on the research smartphone. If there is no reaction to the notification, the app will send additional reminders (about every 3 min). When a notification is accepted and answered, the participants will receive a message that the survey was successful.

Furthermore, the participants will be given containers with Medication Event Monitoring System (MEMS) Caps (AARDEX Group, Liège, Belgium) for the transport and storage of the salivettes. These MEMS Caps are used to improve the adherence to the collection of saliva samples. By opening the containers, the time is registered and controlled. This is also communicated to the participants in advance.

After completing both appointments (T1 and T2), children and adolescents will receive a gift voucher worth 40 euros for their participation. In addition, they will receive another 10 euros if they complete at least 70% in the AA.

### Relevant concomitant care permitted or prohibited during the trial {11d}

Psychiatric, psychotherapeutic, and neurological treatment as well as the use of corticoid-containing and/or psychotropic drugs will not be allowed during study participation, as these correspond to exclusion criteria of our study. Otherwise, there will be no restrictions on concomitant patient care during the trial.

### Provisions for post-trial care {30}

During the test appointment (T2), the participants will be confronted with a stress paradigm in a virtual or real environment, which represents a moderate psychosocial stress induction. We do not expect excessive and long-lasting emotional distress for the participants, since the paradigm resembles everyday school and performance situations and is often used in psychosocial stress research. Furthermore, the participants will be healthy children and adolescents and the participation will be voluntary. If adverse effects (e.g., high stress levels or VR sickness) during the stress induction at T2 occur, they will be noted in detail on a protocol. These adverse effects are, if present, only short term. In this case, the study personnel as psychological experts will always be on site as contact persons. In summary, because we do not expect long-lasting adverse effects beyond the study date, no post-trial care is necessary.

### Outcomes {12}

#### Primary outcome measures

The primary outcome is the comparison of changes in stress responses between the two TSST conditions and relaxation groups. Acute stress reactions will be measured on psychological and physiological level. Self-reported assessments of acute stress / tension, sadness, anxiety / fear, anger, and aggression will be recorded. Moreover, heart rate, cortisol, alpha-amylase, and gaze behavior will be analyzed to compare the changes of these stress responses between the TSST paradigms and the relaxation exercises. In summary, there are several primary outcome variables: mood, cortisol, alpha-amylase, heart rate, and gaze behavior. The reactions will be recorded multimodally to be able to analyze different levels of stress regulation comprehensively.

#### Secondary outcome measures

The second outcome is the change in stress responses in everyday life. Everyday stress reactions will be recorded in the AA via self-report and endocrinological measures at a total of 12 time points. Important variables will be subjective evaluations of sleep quality and quantity, stress / tension, sadness, anxiety / fear, anger, and aggression. Furthermore, the participants will be asked to report stressful events of the day and which coping skills they have used. Cortisol and alpha-amylase will be assessed to analyze endocrinological awakening responses and diurnal hormonal profiles. In summary, there are several secondary outcome variables: mood, cortisol, alpha-amylase, stressful events, coping skills, sleep quality, and quantity.

#### Other outcomes of interest

In addition, personality and temperament traits, intelligence, impulsiveness, aggression, anxiety, trauma, and other psychological variables will be recorded with the help of various psychometric questionnaires and interviews. The variables will be used to characterize the sample and for exploratory correlation analyses, for example, between personality traits and stress responses.

### Participant timeline {13}

In this study, various interventions, questionnaires, and assessments will follow a fixed participant timeline (Fig. 5).

**Fig. 5 Fig5:**
[figure not shown]
Time schedule of enrolment, interventions and assessments. TSST, Trier Social Stress Test; TSST-IV, Trier Social Stress Test in vivo; TSST-VR, Trier Social Stress Test in virtual reality; CFT 20-R, Culture Fair Intelligence Test 20-R – Scale 2; MINI-KID 6.0, Mini-International Neuropsychiatric Interview for Children and Adolescents 6.0; CTQ, Childhood Trauma Questionnaire; PDS, Pubertal Development Scale; JTCI 12-18 R, Junior Temperament and Character Inventory 12-18 R; BFI-10, 10 Item Big Five Inventory; CBCL/6-18R, Child Behavior Checklist 6-18 R (answered by parents and legal guardians); YSR/11-18R, Youth Self-Report 11-18 R; AQC, Alexithymia Questionnaire for Children; VRSQ, Virtual Reality Sickness Questionnaire; IPQ, IGroup Presence Questionnaire; BIS-15, Barratt Impulsiveness Scale – Short Version; BAI, Beck Anxiety Inventory; STADI, State-Trait-Anxiety-Depression-Inventory; CASES, Cognitive, Affective and Somatic Empathy Scales; AQ, Aggression Questionnaire; SSKJ 3-8 R, Questionnaire for the Measurement of Stress and Coping in Children and Adolescents 3-8 R; T0, telephone screening; T1, first test date; AA, Ambulatory Assessment; T2, second test date; T2a, pre-TSST; T2b, TSST; T2c, post-TSST

### Sample size {14}

To estimate the needed sample size, an a priori power calculation was carried out using G*Power [26]. Based on the medium average effect size of a recent meta-analysis of Helminen, Morton, Wang, and Felver [7], an effect size of *f* = .30 was expected. Therefore, a sample size of 84 persons was determined to achieve a power of 95%. Thus, the currently planned study aims at a sample size of *N* = 84. The allocation of participants to the groups will be randomized.

### Recruitment {15}

The healthy participants will be recruited from the Upper Palatinate region in Bavaria, Germany. The recruitment will be done via (online) study flyers, email distribution lists, and advertisements in educational institutions.

## Assignment of interventions: allocation

### Sequence generation {16a}

The participants will be assigned to one of the 4 groups by drawing from a uniform distribution via a pseudo random number generator. A limiting parameter during the assignment process for randomization will be the tolerability of VR. If participants indicate in the screening that they are very susceptible to dizziness (motion sickness), this will be a precautionary criterion for exclusion from the TSST-VR condition.

### Concealment mechanism {16b}

Allocation will be made after the telephone screening. Participants receive a consecutive number which is assigned randomized to one of the 4 groups by the computer software.

### Implementation {16c}

Participants will be registered after they have voluntarily contacted the study management and the inclusion and exclusion criteria have been checked. After completion of T0, study personnel will perform group assignment. For this purpose, the study personnel enters the group number of 4 groups into the pseudo random number generator, which then generates the allocation sequence and assigns the participants to the conditions.

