### Who will take informed consent? {26a}

At the first appointment (T1), a detailed explanation of the study will be provided to the children / adolescents and their parents / legal guardians. This will be done orally and a written information will be handed out additionally. Any questions and uncertainties that arise can be clarified immediately with a person from the study personnel. Consent forms will be signed by the participant, the accompanying parent / legal guardian, and a person from the study personnel. All participants will agree upon taking part voluntarily and termination of their participation is possible at any time without giving any reasons.

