### Intervention description {11a}

After a telephone screening (T0) for checking the inclusion and exclusion criteria, the participants and their parents / legal guardians will be invited to an initial appointment (T1) in our research facilities. Female subjects who are already menstruating will only be tested (AA and T2) in the luteal phase to ensure comparability with the cortisol reactivities to the male subjects [19].

At the first appointment (T1), a detailed briefing for the participants and the parents / legal guardians will be carried out by an experimenter. After answering all upcoming questions and signing the informed consent, an intelligence test and a clinical interview with the participants will be conducted to check the exclusion criteria. Furthermore, the participants will complete questionnaires on puberty status, personality, traumatic experiences, temperament, and behavior. In preparation for the AA, the participants will be instructed in how to use the salivettes (Sarstedt, Nümbrecht, Germany) for collecting saliva samples. Moreover, the usage of the health app including short surveys and the relaxation exercise (developed and programmed in cooperation with the Department of Media Informatics, University of Regensburg) will be explained and demonstrated to the participants. The app was implemented with the integrated development environment Android Studio. The code was written in Kotlin and Java for the target SDK version 29. To develop the questionnaires, the programming library SurveyKit, Version 1.1.0 [20] was used, which is released under the open source MIT License. The application will run on a Samsung A20e with the operating system Android Pie 9.0 installed. Any questions the participant may have regarding the use of the app can be clarified with the experimenter at this point. The first appointment will take approximately 2.5 h.

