## Assignment of interventions: blinding

### Who will be blinded {17a}

Participants will be blinded regarding the objective of the TSST and the relaxation exercise variations. At no time, participants will be aware that there are two relaxation exercises and that they may be in the control group. Participants will know from the recruitment that there is a virtual and a natural setting but are not aware of the composition of the setting.

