## Data collection and management

### Plans for assessment and collection of outcomes {18a}

During the short telephone screening, questions will be asked about schooling, employment, illnesses, and medication intake in order to check the inclusion and exclusion criteria.

To measure stress levels, subjective mood will be registered using 10-item Likert scales that cover the emotional components stress / tension, sadness, anxiety / fear, anger, and aggression (e.g., “At the moment I feel stressed, tensed or charged.”). For the psychophysiological measurement of hormone concentrations, heart rate and gaze behavior, salivettes, electrocardiogram / activity sensors (EcgMove 4 by movisens), and eye-tracking systems (Tobii Pro Glasses 2 and Tobii Eye-Tracking built in HTC VIVE Pro Eye Virtual Reality Glasses) will be used.

During the AA, subjective mood ratings and hormone concentrations of cortisol and alpha-amylase will be measured as mentioned above. Subjective sleep quality / quantity and the evaluation of the day will be assessed by means of morning and evening protocols (e.g., “How good and restful was your sleep?” or “How stressful was today overall?”) [27]. The nature and intensity of stressful events in the domains of family, friends, school, and health since the last survey will be registered at several time points followed by questions on used coping strategies (e.g., “I have recovered.” or “I’ve enlisted help from others.”) [28, 29].

The first test part of the Culture Fair Intelligence Test 20-R – Scale 2 (CFT 20-R) [30] will be used to estimate participants’ intelligence. In general, the test consists of two parts (part 1: 56 items, part 2: 45 items) with four sub-tests each (classification, series, analogies, and matrices).

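### Groups are assigned after the telephone screen, before consent and before the T1 tests that settle eligibility, and no masking of T1 staff is stated

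*Protocol article*

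**What the plan says.** Timing and operator of the allocation are both fixed. Concealment mechanism {16b} says "Allocation will be made after the telephone screening", and Implementation {16c} says "After completion of T0, study personnel will perform group assignment", using a pseudo random number generator that the staff operate.

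Consent comes later. Under the informed consent section {26a}, which describes T1, "Consent forms will be signed by the participant, the accompanying parent / legal guardian, and a person from the study personnel". Intervention description {11a} then says that at the same visit, after consent, "an intelligence test and a clinical interview with the participants will be conducted to check the exclusion criteria". Eligibility criteria {10} shows what these tests decide: current psychiatric disorder (the interview) and an IQ below 85. Under the discontinuation criteria {11b}, a person who meets an exclusion criterion at T1 is taken out of the study there.

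On masking, section {17a} says "Participants will be blinded regarding the objective of the TSST and the relaxation exercise variations". It says nothing about staff. Interim analyses {21b} ends the study when 84 participants have been completely tested.

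**The concern.** Randomisation makes groups comparable at the moment of allocation. Anything that removes people afterwards, and that could depend on the arm, can undo this. Here two filters come after allocation: whether the family consents, and whether the child passes the T1 eligibility tests. The staff who present the study and conduct the interview could know the arm. The analysed sample is then those who passed these filters, topped up to 84, and not everyone who was randomised.

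This touches both comparisons, virtual against real TSST and breathing exercise against natural relaxation. The Discussion relies on the eligibility criteria and on randomisation to deal with sex and age, and that reliance is weaker if the criteria are applied after a group assignment that staff may know.

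**Working it through.** This point is about the order of events, so the check sets the sections side by side.

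| Step | Event | Section of the protocol article |
|---|---|---|
| 1 | Telephone screen (T0) | {11a}, {18a} |
| 2 | Allocation to one of four groups by study personnel | {16b}, {16c} |
| 3 | Consent, at T1 | {26a}, {11a} |
| 4 | Intelligence test and structured interview, at T1 | {11a}, {10} |
| 5 | Removal if an exclusion criterion is met at T1 | {11b} |
| 6 | App and relaxation exercise demonstrated, at T1 | {11a} |
| 7 | Ambulatory Assessment, where the relaxation arm is first used | {11a} |
| 8 | T2, where the TSST arm is first used | {11a} |

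**Is eligibility already settled at step 1?** Section {16c} says that participants are registered after "the inclusion and exclusion criteria have been checked", which could suggest so. But section {18a} describes the call as one in which "questions will be asked about schooling, employment, illnesses, and medication intake in order to check the inclusion and exclusion criteria". Section {11b} adds a question on motion sickness. An IQ score or an interview diagnosis cannot come from such a call, and {11b} expressly foresees exclusions at T1. The check before registration is therefore provisional.

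**Does any step before step 6 need the group?** No. Nothing in steps 3 to 5 is described as differing by arm. Allocation could move from step 2 to just before step 6 without altering any other procedure.

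**Can T1 staff know the group?** Study personnel run the generator, only participants are described as blinded, and the arm-specific exercise is demonstrated at the visit where consent and eligibility are handled. Knowledge is possible. The document does not say that the T1 interviewer made or sees the assignment.

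**How many people might be affected?** The target of 84 is taken as stated in Sample size {14}, and this point does not depend on how it was derived. The document gives no T1 loss rate, so the rates below are assumptions covering exclusions and refusals together. Number allocated = 84 / (1 − loss rate), rounded up.

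- 5%: 84 / 0.95 = 88.4, so 89 allocated and 5 lost after allocation.
- 10%: 84 / 0.90 = 93.3, so 94 allocated and 10 lost.
- 20%: 84 / 0.80 = 105, so 105 allocated and 21 lost.

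These figures count the people exposed to the problem. They do not estimate bias, which would need loss rates and characteristics by arm.

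**The case against.** The strongest defence is that the T1 filters leave little room for discretion. The IQ test is standardised with a numeric cut-off, the interview is structured with yes/no answers, and both measure characteristics that allocation cannot change. If exclusion does not depend on the arm, it costs numbers but creates no selection bias, and any difference between groups is chance. Participants are also not told that two relaxation exercises exist, so they cannot refuse on that ground. They know that a virtual and a natural setting exist, but nothing says that they learn their own before signing. This limits how large the effect is likely to be. It does not remove the route, because staff conduct the interview and the consent discussion and could know the arm.

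A reader might infer that allocation concealment is lost altogether. The document does not support that: each assignment is a random draw from a uniform distribution, so the person screening at T0 cannot foresee it. A reader might also infer that T1 staff do know the group. The document shows only that they could; a condensed article may leave separation of roles to the full protocol.

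Replacement of lost participants is likewise an inference, from the stopping rule in {21b}, but it is hard to read that rule otherwise.

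**Conclusion.** The point holds as one about sequence. Allocation precedes consent and the decisive eligibility tests, so T1 exclusions and refusals fall after allocation, with no stated masking of the staff involved. Confidence in the sequence is high, because each step is written down. Confidence in any resulting bias is low: its direction and size are unknown, and it requires that staff both know the arm and, knowingly or not, act on it. The only available measure of scale, about 94-105 allocated to obtain 84, rests on an assumed loss of 10-20%. The point does not invalidate the trial. It merits a change because the order is a stated rule, the exposure is avoidable and the change is cheap.

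**What to change.** Run the existing random number generator at the end of T1, once consent is signed and eligibility is documented, and just before the arm-specific relaxation exercise is demonstrated. Use the motion-sickness answers from T0 as now. Sections {16b} and {16c} would be reworded to match.

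Recruitment began in June 2021 and was to be complete by January 2023, and this version is dated 5 September 2022, so many participants may already have been allocated. For them, report T1 exclusions and refusals by allocated group, with reasons. Readers can then see whether losses differed by arm.

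The cost is a small scheduling burden, because the T2 set-up is known later, and the eligibility tests must be evaluated within the visit, which the T1 exclusion rule in {11b} already implies. No extra visit is needed. Permuted blocks and a separate person to release assignments are not needed for this fix: blocks do not address timing and can make late assignments easier to guess at a single centre where staff can see the arms, and a release person may need extra staff.
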